**Summary**

High cognitive load of nurses is a common problem in intensive care unit, which is associated with nurses' poor performance of activities, as well as related to poor patient outcomes. It remains unclear whether Artificial Intelligence Assisted Prevention and Management for **Delirium** (*AI-AntiDelirium*) results in reduction of cognitive load and enhances adherence to delirium intervention in ICU nurses. We aim to assess the effectiveness of *AI-AntiDelirium* on cognitive load and adherence to delirium interventions of ICU nurses and the impact of ICU delirium. This is a multicentre, prospective, cluster randomised controlled clinical trial comparing the impact of *AI-AntiDelirium* and PADIS guideline for ICU nurses. A total of six ICUs in two hospital will be randomised in a 1:1 ratio to receive either *AI-AntiDelirium* (intervention group) or PADIS guideline (control group), with target sample size of 78 ICU nurses. The primary endpoint will be the adherence to delirium interventions. The secondary endpoints will be the cognitive load which measured by an instrument for measuring different types of cognitive load (MDT-CL). The endpoints of patients included incidence and duration of ICU delirium, length of ICU and in-hospital stay, ICU and in-hospital mortality. Outcome assessments will be conducted by investigators who blind to group assignment. The repeated measures analysis of variance (RMANOVA) will be performed to detect the difference in adherence and cognitive load between groups. Generalized estimation equation will be performed to

test the difference in patient outcomes.

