### **Study design and setting**

The *AI-AntiDelirium* to improve adherence to delirium intervention of ICU nurses is a multicenter, cluster randomized controlled trial (RCT), six ICUs with higher incidence of ICU delirium in two tertiary hospitals are selected, which represent three types of ICUs (2 Surgical ICU [SICU], 2 Respiratory ICU [RICU] and 2 Cardiac ICU [CICU]) as well as the variety of the samples, and the promise of ICU staff to improve the quality of care in ICU delirium. A tertiary hospital is a 1000-bed university-affiliated teaching hospital, with 42 adult ICU beds in the 3 participating ICUs. B tertiary hospital has 730 beds and 3 eligible ICUs of 46 beds, which the annual admission rate is about 850 patients. They have fully implemented hospital informatization. The study will be conducted during the period 2022 - 2023. Figure 1 shows the design of the study.

[figure not shown]

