### **Sample size**

The aim of the cluster RCT is to improve the adherence to delirium intervention of ICU nurses by using the *AI-AntiDelirium* compared to the PADIS guideline. We expect that adherence to delirium intervention in the *AI-Antidelirium* group is 80% and PADIS guideline group is 50%, suggesting that *AI-Antidelirium* has clinical significance in improving the adherence to delirium intervention of ICU nurses. Sample size calculations showed that 12 nurses in each cluster will provide 80% power and a two-sided significance level ( $\alpha$ ) of 0.05, with an intracluster (within-unit) correlation of 0.002. In addition, taking into account possible dropout rate of 10%, we plan to enroll 13 nurses in each ICU, the final sample size is 78 (13\*6) nurses.

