### **Randomisation**

The risk of between-group contamination is reduced by cluster randomisation, ICUs will be randomised 1:1 to receive either *AI-AntiDelirium* care or PADIS guideline. We plan to recruit 6 ICUs in two hospitals, and matching the types of ICU (considering the different types of ICU nursing process, workload and patients illness severity and other factors which will affect the nurses' adherence). The allocation sequence is based on computer-generated random numbers, which is performed by a statistician who is independent of data analyses and not involved in data collection. In order to ensure the allocation concealment, the statistician will inform the each ICUs' allocation code to the study coordinator. And then, the study coordinator will inform the ICU nurses about which group they are allocated. All eligible nurses are recruited until the sample size is enough.

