### **Statistical methods**

All data will be analysed using SPSS version 21.0 (SPSS Inc Chicago, Illinois) with an intention-to-treat (ITT) principle, missing data will be imputed using multiple imputations. Statistical analyses will be done by a statistician who is blind to intervention allocations. Continuous variables will be described as means and standard deviation (SD) for normally and medians and interquartile range for abnormally distributed data. Comparisons between groups will performed with the Mann-Whitney U-test (analysis of variance) or Wilcoxon test, including cognitive load, adherence, duration of ICU delirium, length of ICU stay, length of stay in the hospital. Categorical variables will be expressed as frequencies and percentages. Chi-Square test or Fisher's exact test will used to examine between-group differences among incidence of delirium, baseline delirium risk factors and demographics.

Considering the correlation that results from repeated measurements on the same individual, repeated measures analysis of variance (RMANOVA) is used to analyze the multiple measurements variable which is gathered on everyday, such as CL,

adherence of ICU nurses. We will adjust for age, educational level, years of ICU experience, level of knowledge, since these factors were likely to be associated with adherence and CL. Bonferroni post hoc tests were used to assess within-group changes over time, as well as between-group differences during study intervention. Differences in incidence of delirium between groups are analyzed after adjusting for demographic variables using generalized estimation equation. All tests are two-tailed, and P - value < 0.05 is considered statistically significant.

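### Tests of patient endpoints ignore the randomised ICU, and the GEE cluster is unnamed, so p-values for delirium and length of stay are too small by an amount the protocol cannot fix

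*Protocol*

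**What the plan says.** The ICU is the unit of randomisation: "A total of six ICUs in two hospital will be randomised in a 1:1 ratio" (Summary). The Randomisation section adds that "We plan to recruit 6 ICUs in two hospitals, and matching the types of ICU"; Study design and setting lists two surgical, two respiratory and two cardiac ICUs.

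Statistical methods gives three analyses that touch patient endpoints:

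- Chi-square or Fisher's exact test "will used to examine between-group differences among incidence of delirium, baseline delirium risk factors and demographics".
- Mann-Whitney or Wilcoxon tests for duration of delirium, ICU stay and hospital stay (and also for cognitive load and adherence).
- GEE for incidence: "Differences in incidence of delirium between groups are analyzed after adjusting for demographic variables using generalized estimation equation".

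None of these has an ICU term. The only correlation the section mentions is that between repeated measurements on one person. The significance rule is general: "All tests are two-tailed, and P - value < 0.05 is considered statistically significant".

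The Summary gives GEE a wider role. Its sentence begins "Generalized estimation equation will be performed to" and goes on to cover patient outcomes as a group, where Statistical methods confines GEE to incidence.

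The Sample size section does include a within-unit correlation (0.002), but only for nurse adherence. No patient number and no ICC for a patient outcome appear anywhere.

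**The concern.** Patients in one ICU share staff, case mix and routines, so their outcomes are likely to be correlated. With whole ICUs randomised, that correlation adds to the variance of the difference between arms. A chi-square or Mann-Whitney test leaves it out, so its standard error is too small whenever the within-ICU correlation is positive.

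GEE could deal with this, but only if the ICU is its cluster and the inference allows for there being just six. The protocol says neither. If the cluster is the nurse or the patient, ICU correlation is again ignored.

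The Background names clinical outcomes related to delirium among the trial's aims. A statement that the system lowers delirium or shortens stay would rest on these tests.

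**Working it through.** **The protocol's own figure first.** The sample size already uses a cluster design effect. Inputs: 80% v 50% adherence, two-sided 0.05, 80% power, ICC 0.002, six ICUs. The unpooled formula gives (1.96 + 0.842)² × (0.16 + 0.25) / 0.30² = 35.76 nurses per arm. The design effect is 1 + (12 − 1) × 0.002 = 1.022, so 35.76 × 1.022 / 3 = 12.2 per ICU, which agrees with "12 nurses in each cluster will provide 80% power" (power 79.4% at 36 per arm). Clustering by ICU is thus recognised at the design stage for nurses but absent from the tests of patient endpoints.

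**Tests that ignore the ICU.** With m patients per ICU and intracluster correlation ICC, the design effect is DE = 1 + (m − 1) × ICC. The true type I error of a nominal 5% test is 2 × [1 − Φ(1.96/√DE)]. With m = 70 (assumed) and no gain from matching:

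| ICC | DE | 1.96/√DE | Rejection under no effect |
|---|---|---|---|
| 0.002 (protocol, nurse adherence) | 1.138 | 1.837 | 6.6% |
| 0.01 (assumed) | 1.69 | 1.508 | 13% |
| 0.02 (assumed) | 2.38 | 1.270 | 20% |
| 0.05 (assumed) | 4.45 | 0.929 | 35% |

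Range over other sizes, from 20 to 200 patients per ICU: 5.4% to 9.7% at ICC 0.002, 7.2% to 25.7% at 0.01, and 16.0% to 55.4% at 0.05.

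The only volume figure is about 850 admissions a year at hospital B. If that refers to its three ICUs, the eight months from November to June give 850/3 × 8/12 ≈ 190 per ICU. At 190 the formula gives about 9.5% (ICC 0.002) and 25% (ICC 0.01), so 70 is not a high assumption.

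Simulation (3 v 3 ICUs, unmatched, 30% incidence assumed for the binary outcome) agrees. With 100 patients per ICU, chi-square rejected 16.7% at ICC 0.01 and 42.0% at 0.05 (formula: 16.5% and 42.2%). Mann-Whitney on log-normal stays rejected 16.2% and 42.3%.

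**GEE with the ICU as cluster.** With an uncorrected sandwich variance and a normal reference, simulated rejection was 17.6% to 18.8% for ICCs from 0 to 0.10 and 20 to 150 patients per ICU. The cause is having six clusters, so the figure hardly moves with the ICC. Fitted exchangeable logistic GEE with two covariates gave 14% to 20% over six settings of 400 runs each (Monte Carlo standard error √(0.18 × 0.82/400) ≈ 1.9 points).

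**GEE with the patient or nurse as cluster.** Correlation between patients of one ICU is not modelled across those clusters, so the problem of the unclustered tests remains.

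**A method that holds its level.** A t-test on six ICU-level proportions (4 df, unmatched) rejected 4.6% to 5.4% in every setting. An exact permutation test is not an option at 0.05: its smallest two-sided p-value is 2/20 = 0.10 for unmatched 3 v 3 and 2/8 = 0.25 for three matched pairs.

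**The case against.** Several points on the other side have force.

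- **Size.** A reader might infer that the p-values are shown to be far too small. The protocol does not support that for every test. Patient numbers and patient ICCs are assumptions, and at the one ICC it states the unclustered tests run only slightly above 5%. That ICC was set for nurse adherence, however, so it neither shows nor excludes small clustering of patient outcomes.
- **GEE.** A reader might infer that GEE fails however it is read. The 18% needs three things the protocol does not state: the ICU as cluster, an uncorrected sandwich and a normal reference. A small-sample correction may properly sit in a statistical analysis plan that is not at hand, and its absence is not held against the protocol. What stands is that the cluster is unnamed and the only correlation mentioned is within a person.
- **First-step comparisons.** The chi-square and Mann-Whitney sentences also cover baseline variables or nurse outcomes, and incidence gets a later GEE, so they might be preliminary. This is fair for incidence. It does not help delirium duration or lengths of stay, for which Statistical methods names no other model, and the 0.05 rule applies to all tests.
- **Matching.** If ICUs were allocated within type pairs, differences between ICU types would largely cancel between arms and the inflation at a given overall ICC would be smaller. This stands. The calculations are for an unmatched design.
- **Importance.** Adherence is primary and cognitive load secondary; patient endpoints appear in the Summary but not in the Outcomes section or Table 1. This limits the weight of the point but does not remove it.

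**Conclusion.** Wrong as written, and not merely short of detail: the protocol prescribes tests that treat patients as independent in a trial that randomises ICUs, and its two accounts of where GEE applies disagree.

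Confidence is high on direction, given any positive within-ICU correlation left after matching. It is moderate on size. The unclustered rates depend on the assumed patients per ICU, the assumed ICC and an unmatched design. The GEE rate depends little on the ICC, but it does depend on the three unstated conditions and was likewise obtained without matching. The documents support p-values that are too small, possibly by a wide margin; they do not support a single figure for the excess.

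**What to change.** In Statistical methods:

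1. Name the ICU as the cluster for every patient endpoint.
2. Use a small-sample method. The simplest is ICU-level summaries, covariate-adjusted where wanted, compared by t-test: 4 df if allocation was unmatched (6 − 2), 2 df if it was within ICU-type pairs (3 − 1). State which applies.
3. Alternatively use a mixed model with an ICU random intercept, or GEE clustered on the ICU with a bias-corrected sandwich (Kauermann-Carroll or Fay-Graubard). Either needs matching small-sample df and few covariates. Neither was successfully checked by simulation here, so confirm its type I error with six clusters before adoption.
4. Label chi-square, Fisher, Mann-Whitney and Wilcoxon results on patient endpoints as descriptive.
5. Make the Summary and Statistical methods agree on which endpoints GEE, or its replacement, covers.

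The nurse-endpoint analysis cannot serve as a template: the repeated measures ANOVA described there handles correlation within a person, not within an ICU.

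The change is to wording only and needs no new data. The cost is wider intervals and little power for patient endpoints with six ICUs, most of all on 2 df.

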**Figure 1. Modules of Application**

A: ICU delirium assessment tools and results; B: risk factors assessment and predictive risk value;  
C: nursing care plan; D: nursing checklist

ICU nurses in the intervention group will provide ICU delirium nursing care based on *AI-AntiDelirium*. Each day, the nurse will assess ICU patients with the assistance of *AI-AntiDelirium*, which can recognize ICU delirium, automatically

present risk factors and tailor evidence-based prevention or management strategies of ICU delirium. During the study, the nurse who receive ICU delirium training clicks the icon of *AI-AntiDelirium* on the Personal Digital Assistant (PDA) to enter the system.

- a. **Register:** click the icon of register → enter the user name → enter the password → choose the hospital and department → submit;
- b. **Log in:** enter the user name and password → log in.
- c. **Add the patient:** click the button “+” → enter the medical record No. → enter patient name → enter patient gender → enter patient age → enter patient bed number → enter patient admission time.
- d. **Diagnose ICU delirium:** click the button of delirium assessment → select a delirium assessment tool (CAM-ICU or ICDSC) → complete the item one by one according to the prompts → the *AI-AntiDelirium* will automatically display whether the patient has delirium or not.
- e. **Identify patients ICU delirium risk factors:** click the button of “risk factors assessment” → complete a brief risk factor assessment evaluation list, including three categories, predisposing (e.g. hearing impairment, vision impairment), disease-related (e.g. infection, pain), iatrogenic and environmental factors (e.g. mechanical ventilation, sedative use) → the *AI-AntiDelirium* will automatically report personalized risk factors of the patient → the *AI-AntiDelirium* will automatically show the risk prediction value in developing delirium according to a dynamic ICU delirium prediction rule.
- f. **Confirm nursing care plan:** click the button of “nursing care plan” → the *AI-AntiDelirium* will automatically present individual ICU delirium prevention or management care plan according to the result of risk factors assessment → the ICU

nurse checks and confirms that all interventions for the patient are appropriate and feasible.

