### **Control group**

Prior to the study, an educational program related to ICU delirium is delivered by researchers, the content are same to intervention group. In addition, nurses are trained with the usage of PADIS guideline. During the study, nurses will provide ICU delirium nursing care according to PADIS guideline, including ICU delirium risk factors, assessment tools (CAM-ICU, ICDSC), and ABCDEF bundle intervention.

a. **Diagnose ICU delirium:** The nurse chooses one instrument (CAM-ICU or ICDSC) to assess ICU delirium occurrence and completes the item one by one. The nurse manually records the assignment score of each item, and calculates the final total score, and then they judge whether the patient develops delirium or not according to the rule of assessment tool.

b. **Identify patients ICU delirium risk factors:** The ICU nurse fills out a brief risk factor assessment for delirium (the content same to intervention group). The nurse makes decision by themselves about patient's current risk factors according to the risk factors assessment results and manually calculates the patient's current risk of developing ICU delirium according to the dynamic ICU delirium prediction rule.

c. **Implement individual, risk factors targeting interventions:** The nurse extracts nursing intervention from the PADIS guideline according to the result of patient' specific risk factors, and records the intervention in nursing care records, and implements appropriate subset of interventions.

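### The delirium-incidence GEE adjusts for demographics only: baseline delirium risk factors are tested but not modelled, and the matching factor, ICU type, is left out

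*Protocol*

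**What the plan says.** The Statistical methods section of the protocol gives one adjusted analysis for a patient outcome: "Differences in incidence of delirium between groups are analyzed after adjusting for demographic variables using generalized estimation equation". It names no delirium risk factor, severity measure, ICU type or hospital for that model.

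Baseline risk factors appear in the same section in one role only: "Chi-Square test or Fisher's exact test will used to examine between-group differences among incidence of delirium, baseline delirium risk factors and demographics".

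Risk information is produced in both arms during care. Under Intervention Groups, step e, nurses "complete a brief risk factor assessment evaluation list, including three categories, predisposing" and other factors, and the system will "automatically show the risk prediction value in developing delirium". Under Control group, step b, the wording is "The ICU nurse fills out a brief risk factor assessment for delirium (the content same to intervention group"), and the nurse works out by hand the patient's "current risk of developing ICU delirium according to the dynamic ICU delirium prediction rule".

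On design, the six ICUs are chosen as units "which represent three types of ICUs (2 Surgical ICU [SICU], 2 Respiratory ICU [RICU] and 2 Cardiac ICU [CICU"]). The Randomisation section allocates them 1:1 and matches on ICU type, with patients' illness severity among the reasons. Study design and setting places three of the ICUs in each of two hospitals.

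**The concern.** Patients are not individually randomised. They take the allocation of the ICU that admits them, and there are only three ICUs per arm. Allocation on that scale cannot be relied on to even out patient risk, so baseline predictors of delirium are the natural covariates for this outcome.

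The protocol follows that logic for the nurse outcomes, where it adjusts for factors because they are likely to be related to adherence and cognitive load. For delirium it does not. It tests the risk factors for a difference between arms and then fits a model without them. A significance test of baseline differences leaves the treatment estimate as it was, whatever its p-value. Leaving out the matching factor also means that the analysis does not reflect the design.

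At stake is the precision and credibility of the delirium comparison, which is one of the trial's stated aims but not its primary outcome.

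**Working it through.** **The plan's own figure.** There is none for delirium. The only sample-size calculation concerns nurse adherence and does not bear on this point.

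**Inputs from the protocol.** Six ICUs, two of each of three types, allocated 1:1, so three per arm. I read the matching as one ICU of each type in each arm. Each hospital supplies three ICUs. Three is odd, so within a hospital the split between arms is 2:1 at best, and matching on type cannot balance hospital.

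**Inputs assumed.** Incidence p of 30% or 70%. The Background cites 70% to 87%, so 87% is shown as well. Between-ICU SD of risk on the logit scale, s, is 0.3, 0.5 or 0.8. The share f of that variance explained by ICU type is 0 (matching achieves nothing), one half or three quarters. There is no true treatment effect and no patient-level sampling error.

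**Formula.** With type balanced across arms, only the unexplained part contributes to the difference between two three-ICU means:

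SD(difference) ≈ p(1−p) × s × √(1−f) × √(2/3)

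Example with p = 0.30, s = 0.5, f = 0.5: 0.21 × 0.5 × 0.707 × 0.816 = 0.061. The chance of a gap above 5 points is 2Φ(−0.05/0.061), about 0.41. Simulation of the ICU risks on the logit scale gives SD 0.059 and probability 0.40.

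**Simulated chance of a gap above 5 points with no effect, for s = 0.3 / 0.5 / 0.8**

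| Incidence | f = 0 | f = 0.5 | f = 0.75 |
|---|---|---|---|
| 30% or 70% | 33 / 55 / 70% | 17 / 40 / 58% | 5 / 23 / 44% |
| 87% | 8 / 30 / 53% | 2 / 15 / 38% | <1 / 5 / 23% |

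At 30% incidence the SD of the gap is 5.1 / 8.4 / 12.8 points for f = 0 and about 3.6 / 5.9 / 9.1 points for f = 0.5. The results for 30% and 70% agree by symmetry.

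**What one omitted factor does.** Assume a binary risk factor with 40% average prevalence and an odds ratio of 2 to 3 for delirium, and a risk of 20% to 70% without the factor. Example: risk 30% without the factor and odds ratio 3 give 56.25% with it. Prevalences of 35% and 45% give arm risks of 0.65 × 0.30 + 0.35 × 0.5625 = 0.392 and 0.55 × 0.30 + 0.45 × 0.5625 = 0.418, an odds ratio of 0.90 with no treatment effect. Over the assumed ranges:

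| Prevalence gap between arms | Spurious odds ratio |
|---|---|
| 0 points | 1.00 |
| 5 points | 0.95–0.97 |
| 10 points | 0.90–0.94 |
| 20 points | 0.80–0.88 |

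**Are the covariates available?** Statistical methods presupposes baseline delirium risk factors. Data collection and Table 1, however, list baseline items for nurses only, and in Table 1 the risk-factor assessment is an intervention step. Those nurse-recorded values come after allocation, from staff who cannot be blinded, and are automated in one arm and manual in the other. Completing them is also a component of the primary outcome (Outcomes, item b), so missingness may differ by arm.

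**The case against.** Four objections deserve weight.

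- **Matching.** A reader might infer that six non-comparable ICUs are being contrasted. The protocol does not support that: ICUs are matched on type, partly for illness severity, so the most obvious source of case-mix difference is handled by design. What remains is difference within pairs, including hospital. The 33 / 55 / 70% figures ignore the matching and are only an upper bound.
- **Chance, not systematic bias.** Allocation is random, so leftover risk differences are between-cluster variation that a properly clustered analysis should carry in its standard error. This stands. It does not remove the case for adjustment, because six clusters make that standard error weak and prognostic covariates reduce the variation itself. The figures above cover all between-ICU variation, however. Adjustment removes only the part that measured factors explain, and the documents give no way to say how much.
- **Availability.** A reader might infer that the data are already in hand. That is only partly supported: the analysis text presupposes them, but no schedule collects them, and the nurses' scores are poor covariates.
- **Detail left to an analysis plan.** Exact covariate lists often are. Here, though, the protocol itself fixes the kind of covariate (demographic) and gives the risk factors a different use, so the point rests on what is written.

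**Conclusion.** The point holds as a worthwhile improvement to a patient-outcome analysis. The protocol names prognostic baseline variables, uses them only in a test that cannot correct imbalance, and omits the matching factor from the model. Chance differences in patient risk can therefore add noise to the delirium comparison.

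For a gap above 5 points with no effect, a reasonable illustration is about 17%, 40% or 58%. This assumes 30% or 70% incidence, a between-ICU logit SD of 0.3, 0.5 or 0.8, and type explaining half the variance. The figures are lower if type explains more or incidence is near 87%. None of these inputs except the cited incidence range comes from the documents, so the size is conditional.

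A reader might go further and infer that the delirium result will be biased or that the trial's main conclusion is at risk. Neither follows. The imbalance is a matter of chance, and nurse adherence, the primary outcome, is analysed separately.

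**What to change.** In Statistical methods, pre-specify for the delirium GEE a short list of admission delirium risk factors, or a single baseline predicted risk built from them, together with ICU type. State that the values are those at ICU admission, recorded in the same way in both arms by the blinded data collectors, and not the nurses' daily scores. Add these patient items to Table 1. Between-group tests of the baseline risk factors should not stand in for adjustment.

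The cost is modest: one scheduled admission data item per patient, some missing values for the planned multiple imputation, and a few lines of text. The list must stay short. Six clusters less two arm means leave 4 degrees of freedom at cluster level, and a three-level ICU type uses 2 of them. A single patient-level risk score is therefore attractive, and it can also pick up measured differences between hospitals. Adjustment does not cure the unreliable GEE standard errors that come with so few clusters; that needs its own remedy.
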